**Abstract**

*Since 2008, the Government of the DRC launched a national program known as National Healthy Villages and Schools (in French Villages et Ecoles Assainis, VEA), a water and sanitation program financed by DFID and implemented by UNICEF and the Government of DRC’s Ministry of Public Health and Ministry of Primary, Secondary, and Professional Education. The VEA’s main objectives are to support communities’ improved access to water, hygiene, and sanitation services and practices through the construction of water and sanitation infrastructure in villages and schools, local community involvement, and a village certification mechanism. This study uses a cluster-level randomized controlled trial to evaluate the causal impact of the VEA program across 332 rural villages implemented in the later phase of the program (throughout 2019). It involves experimentally varying the provision of the VEA program to a set of villages to examine the causal impacts on water access, infrastructure development, availability of sanitation services, knowledge of hygiene practices, and child health. Program impacts will be ascertained on a wide-range of key outcomes of interest, including water quantity and quality; health behavior/knowledge, time use, child health, and school attendance.*

**Keywords:** Community-Driven Water, Sanitation and Hygiene**; rural communities; conflict settings; cluster-randomized control trial; Democratic Republic of Congo.**

# **Introduction**

Rural WASH is inadequate in many developing countries, especially those affected by fragility, conflict and violence (FCV), with important implications for human welfare. This is the case in the Democratic Republic of Congo (DRC)— home to approximately 80 million people, including 7% of the world’s extreme poor. Seventy percent of the population is rural, and many residents have experienced protracted instability and violent conflict. The DRC ranked 176^th^ in the Human Development Index in 2015, with a life expectancy of 59.1 years and an adult literacy rate of 77%. The under-5 mortality rate is 104 per 1,000 live births (118 in rural areas). Only 31% of rural Congolese use an improved water source and only 29% use improved sanitation facilities (UNICEF/WHO JMP 2015). 59% of rural households spend more than 30 minutes (on each round trip) to collect drinking water.

Against this backdrop, in 2008, the Government of the DRC launched a national program known as the “National Healthy Village & Schools Programme” (in French, *Villages et Ecoles Assainis-VEA*), a Water and Sanitation (WASH) program financed by DFID and implemented by UNICEF and the Government of DRC’s Ministries of Public Health, and Primary, Secondary, and Professional Education. The VEA’s main objectives are to support improved access to water, hygiene and sanitation (WASH), especially in rural areas. The VEA supports the construction of water and sanitation infrastructure in villages and schools, facilitates local community involvement in management of this infrastructure, conducts behavior change activities, and then formally certifies communities (as “Healthy Villages” or “Healthy Schools”) when they achieve a set of water and sanitation norms. Since 2008, approximately 6,500,000 people in several thousand villages have been reached with WASH services through the program (UNICEF 2017). The program is currently in Phase 2 (2013-2018) which, to support this impact evaluation, will offer an extended VEA programme to an additional 240 villages and 60 schools in 5 provinces (Kongo Central, Kasai, Kasai Central, South Kivu, North Kivu).

Given the strategic importance of the VEA as one of DFID’s biggest investments in the WASH sector, accounting for over 50 percent of its DRC budget in this sector, and the largest WASH program implemented by UNICEF globally, the Development Impact Evaluation Unit (DIME) of the World Bank’s Research Group is partnering with DFID and UNICEF to conduct a rigorous evaluation study, which will provide scientific evidence of the effects of the VEA program. Specifically, this evaluation study entails both an impact evaluation that seeks to ascertain the program’s impacts on key outcomes of interest, and a process evaluation that focuses on specific program elements (e.g., coordination among different stakeholders, sustainability, and the extent of community involvement) that are crucial to the implementation strategy. The study will also comprise in-depth qualitative research to unpack processes and mechanisms that underlie the functioning of the VEA program. This study will present robust evidence to improve policy decisions pertaining to WASH policies and programs in the DRC and beyond.

This pre-analysis plan focuses on the impact evaluation component of the study, with a specific focus on the outcomes that will be measured in a midline survey. Given the short time between program completion and fielding of the midline survey, we primarily measure program implementation in this survey. The endline data collection will likely include additional outcomes and measurement strategies, including an expanded sample to increase power on key development outcomes which will be specified at a later stage and documented in an addendum to this pre-analysis plan. This pre-analysis plan focuses on the midline survey, which means that we focus on a more limited set of outcomes, primary relating to water access and program implementation, than in the eventual endline survey, which will be a large survey with more detailed measurement of health outcomes.

# **Hypotheses/Evaluation Questions**

The primary hypotheses this evaluation seeks to investigate pertain to the impact of the VEA program on key outcomes of interest, including: (i) access to higher quality water and improved sanitation; and (ii) reduced burden of collecting and carrying water (measured by time used for collection) especially for women and girls.

More formally, we propose to test the following primary hypotheses using the midline data:

*Hypothesis 1: VEA will improve households’ water quality*

*Hypothesis 2: VEA will improve sanitation facilities that households use*

*Hypothesis 3: VEA will increase the quantity of water that households use*

*Hypothesis 4: VEA will reduce the time spent collecting water*

In addition, there are several secondary hypotheses of interest implied by the theory of change. They address potential health and education outcomes and the mechanisms by which the inputs from VEA could produce the desired outcomes. Improvements in the water sources and in the point-of-use are related to the reduction of diarrhea, but effects can be larger if purification treatments are sustained over time (Shimamura et al. 2017). As for the participation of community members in leading the WASH projects, a study of the Community-Led Total Sanitation (CLTS) in Ethiopia and Ghana found that community engagement-led training of local leaders reduced open-defecation (Crocker et al. 2011). Another evaluation of community involvement in WASH projects in Bangladesh found that handwashing after defecation significantly improved among men, but hygiene practices before preparing, serving or eating food remained extremely low (Johnston et al. 2009). Taken together, these studies call for finding and testing the best ways to assure that the program can lead to more effective WASH governance, more sustained functionality of WASH infrastructure, reduced cost of water, and more effective community involvement including via sustained behavior change, such that the program can translate into water and sanitation gains for individuals and households. Thus, this study will also investigate the following hypotheses^[[1]](#footnote-1)^:

*Hypothesis 5*: *VEA will increase the number of functional water points in a village*

*Hypothesis 6*: *VEA will reduce the cost of water*

*Hypothesis 7*: *VEA will increase satisfaction with access to water*

*Hypothesis 8*: *VEA will increase the probability that a village has a committee that is responsible for water*

*Hypothesis 9*: *VEA will increase the frequency with which health zone representatives visit a village*

*Hypothesis 10*: *VEA (via the behavioral change encouragement activities) will increase the frequency of improved health behaviors*

Program impacts of water and sanitation interventions have a mixed track record. Particularly for sanitation, the current experimental evidence has a wide variety of results, including many null results for diarrhea, which has often been identified as a primary outcome for these studies (Whittington et al, 2020). Reflecting on this, the research takes a cautious approach to measuring impacts. In the midline we will run exploratory analysis on health and education outcomes driven by the following hypotheses:

*Hypothesis 10: VEA will increase children’s school attendance, conditional on their enrollment*

*Hypothesis 11: VEA will reduce the incidence of diarrhea for U5 children*

The longer-term follow up survey will expand the set of outcome measures, which will be described in detail in the updated PAP.

# **Study Design**

## Treatment and Control Groups

Our goal is to estimate the causal effects of the core VEA program with a randomized control trial. The unit of treatment is the village; thus, a straightforward randomization would be at the village level. However, VEA villages can be quite close to one another, raising the possibility of spillover effects from treatment villages to control villages (e.g. people in control villages accessing new water points in treatment villages). Therefore, we grouped villages into clusters. We considered any villages within 2.5 km of each other (with distance determined “as-the-crow-flies”) to be part of the same cluster. Therefore, all clusters have at least 2.5 km between them. We relax this rule in South Kivu, where density is greater and we seek to include naturally occurring villages, rather than the smaller unit of VEA sub-villages, in the sample. In cases where naturally occurring/administrative villages are less than 1 km from each other, we aggregate these into a single village cluster.

UNICEF generated and shared with the research team a list of 403 candidate villages based on the established criteria for the program: the village is located in a secure and accessible Health Area that is not already served by the WASH Consortium, the Health Area staff are dynamic and interested in participating, and there is a problem of diarrhea, cholera, and/or malnutrition.^[[2]](#footnote-2)^ Thirty-four of these villages were already in process (in Kasai Central), leaving 369 eligible villages in five provinces: Kongo Central, Kasai, Kasai Central, South Kivu, and North Kivu. Based on the rules above, we grouped those villages into 124 clusters. North Kivu had only three clusters (covering 30 villages), so we decided that it was not logistically efficient to work there. That left us with 121 clusters in four provinces and 339 villages.

We randomized these into 50 treatment clusters (containing 146 treatment villages) and 71 control clusters (containing 187 control villages). Six villages were randomly dropped to ensure UNICEF target numbers were met, while maintaining treatment and control balance.^[[3]](#footnote-3)^ We stratified randomization to ensure that the treatment and control groups are balanced with respect to their (i) province and (ii) number of villages that make up a cluster. Stratified randomization ensures that the treatment and control groups will be statistically indistinguishable from each other with respect to these characteristics, thereby avoiding bias in treatment effect.

Treatment clusters of villages will receive the status quo VEA intervention, as described above. Control clusters of villages will not receive any intervention from VEA. Data collection procedures will be identical in the two groups, as described below.

Additional discussions were held regarding the possibility of overlaying the school intervention as part of the impact evaluation. Due to the fact that the schools had been pre-selected in each province, this was not possible. There is, however, some possibility that the school intervention is differentially implemented in proximity to treatment and control villages which could threaten the validity of the results, particularly on schooling-related outcomes.

The IE team will work closely with UNICEF and local implementing partners to ensure accurate GPS and implementation tracking information is included in the planned data collection exercises to ensure that, if imbalance in proximity to treatment schools does occur, we will be able to adequately control for this in the analysis.

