# **Appendix**: Randomization Annex

UNICEF provided DIME with a set of 403 georeferenced villages across the 5 districts of Kongo Central, Kasai, Kasai Central, South Kivu and North Kivu, where villages were defined based on the EVA program definition. From this dataset, 34 villages from Kasai Central were already indicated to have been assigned to receive the program, leaving a universe of 369 program villages to conduct the randomization. The main requirements that were imposed on the randomization were:

1. The number of treatment villages needed to match exactly with the number of UNICEF target villages for the program in each province.
2. Due to concerns of possible spillovers, the randomization needed to cluster villages deemed to be too close to each other.

*What were the clustering rules used?* In rural provinces (Kasai, Kasai Central and Kongo Central) any village within 2.5km (as the crow flies) of another village would be considered as part of the same cluster. This was discussed as an appropriate distance to avoid meaningful spillovers since it would imply an approximately 45-minutes one-way journey to the program water source on average which far exceeds the SDG definition of improved water requiring that a round trip take 30 minutes or less. The more densely populated urban areas (South and North Kivu) require a modified clustering rule to avoid all villages joining a single cluster. Here the procedure is to cluster all program villages that belong to the same administrative villages into single clusters (i.e. consider the administrative village rather than the program village as the unit of randomization). However, some administrative villages lie very close to one another. As an additional level of clustering, we then combine all administrative villages that lie within 1km of each other^[[5]](#footnote-5)^.

Once clusters are identified, we randomize clusters into treatment and control groups, stratifying by province and cluster size to ensure balance. In all provinces except Kasai Central, each cluster is given equal probability of being selected for treatment or control. In Kasai Central, we increase the probability of being selected into the control group proportionally to reflect the fact that only 16 out of 81 villages from the sampling frame were required to be assigned to receive treatment.

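### The 2.5 km buffer does not cover the 34 Kasai Central villages already in process for VEA, and the planned spillover check may not see exposure of controls to them

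*Protocol*

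**What the plan says.** The protocol (Study Design, Treatment and Control Groups) recognises that control households might fetch water from new points in nearby treated villages, and it answers this with distance-based clusters. The order of the steps is what matters here. First come the exclusions: "Thirty-four of these villages were already in process (in Kasai Central), leaving 369 eligible villages in five provinces". The Randomization Annex gives the same step: "34 villages from Kasai Central were already indicated to have been assigned to receive the program, leaving a universe of 369 program villages". Only then are clusters formed: "Based on the rules above, we grouped those villages into 124 clusters". In Kasai Central the rule was that "any village within 2.5km (as the crow flies) of another village would be considered as part of the same cluster", and the resulting assurance is "Therefore, all clusters have at least 2.5 km between them", with a relaxed rule for South Kivu.

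The control condition is no VEA intervention. Under Subgroup And Spillover analysis, the protocol gives the possible closeness of clusters in South Kivu as the reason for a spillover check. The check compares control households that have more, or fewer, intervention households within 2 km. A footnote calls it a robustness check. The same section lists province among the exploratory subgroups for the primary outcomes. The annex notes that the full list was georeferenced: "UNICEF provided DIME with a set of 403 georeferenced villages".

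**The concern.** The 34 villages are on the same candidate list, in the same province and destined for the same programme as the treatment villages. For a control household choosing where to fetch water, a VEA point in one of them is no different from one in a randomised treatment village. Yet the protocol sets no minimum distance from them, flags no control village near them and plans no adjustment for them. The only proximity adjustment it foresees concerns VEA schools.

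Such use would raise the control level of improved-source use and could shorten collection time. Treated villages would gain less from the same neighbours because they have points of their own. The contrast would shrink in Kasai Central, and a weaker result there could be read as genuine variation between provinces. There is no baseline survey to show which households already used neighbouring points.

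**Working it through.** **1. Village flow (Treatment and Control Groups; annex table).**
- 403 − 34 = 369; 369 − 30 (North Kivu) = 339; 339 − 6 dropped = 333 = 146 + 187.
- Clusters: 124 − 3 = 121 = 50 + 71.
- Province frames: 40 + 98 + 81 + 120 = 339.

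The protocol's counts reproduce. The 81 Kasai Central villages in the table therefore exclude the 34, and the 34 are in none of the 124 clusters.

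**2. Share of Kasai Central in each arm.**
- Control: 65/187 = 35% of villages; 29/71 = 41% of clusters.
- Treatment: 16/146 = 11% of villages; 8/50 = 16% of clusters.

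**3. Weight of Kasai Central in the pooled estimate.** The Estimation section includes stratum dummies, so each stratum contributes roughly in proportion to nT × nC / (nT + nC). The cluster-size strata are not listed, so this is done by province.

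| Province | By villages | By clusters |
|---|---|---|
| Kongo Central | 20×18/38 = 9.47 | 9×9/18 = 4.50 |
| Kasai | 50×44/94 = 23.40 | 20×19/39 = 9.74 |
| Kasai Central | 16×65/81 = 12.84 | 8×29/37 = 6.27 |
| South Kivu | 60×60/120 = 30.00 | 13×14/27 = 6.74 |
| Kasai Central weight | 12.84/75.72 = 17% | 6.27/27.26 = 23% |

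**4. Dilution.** Let f be the share of Kasai Central control households that gain the full VEA effect from the 34 villages. The documents give no value for f, so a range is shown. The Kasai Central effect retained is 1 − f. The pooled effect retained is 1 − w × f, with w = 0.17 or 0.23.

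| f (assumed) | Kasai Central effect retained | Pooled effect retained |
|---|---|---|
| 0 | 100% | 100% |
| 0.10 | 90% | about 98% |
| 0.25 | 75% | 94–96% |
| 0.50 | 50% | 88–92% |
| 1 | 0% | 77–83% |

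**5. Can the planned check see it?** Study clusters in Kasai Central are at least 2.5 km apart, and the check looks within 2 km. If only randomised treatment villages count as exposure, a Kasai Central control household has essentially none, so the more-versus-fewer comparison is empty there. If the 34 are counted, the check can work, but it still misses those lying between 2 and 2.5 km away. The text does not say which count is meant.

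**The case against.** The strongest reply has four parts.

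- **Validity.** The 34 were fixed before randomisation, so closeness to them is balanced between arms in expectation, and the estimate remains valid as the effect of assignment given existing VEA coverage. This stands: randomisation is not broken. The estimate does, however, move away from a comparison with no access to VEA points, which the clustering was meant to protect.
- **Detection.** A reader might infer that dilution would pass wholly unnoticed. That goes too far. The province subgroup would show a weaker Kasai Central effect, though not its cause, and the wording of the spillover check does not exclude the 34.
- **Status.** A reader might take the 34 as already served. The texts say only that they were in process and, in the annex, that "34 villages from Kasai Central were already indicated to have been assigned to receive the program". Working points by midline are a natural expectation but are not documented.
- **Size.** The annex treats 2.5 km as about 45 minutes one way, so it is a cautious buffer and not a radius of routine use. At that pace a 30-minute round trip reaches 2.5 × 15/45 = 0.83 km. One can model the 34 as scattered evenly among the study villages, in a 32 km square that reproduces about 37 clusters. About 46% of the 81 study villages then lie within 2.5 km of one of the 34, but only 1 − exp(−34/1024 × π × 0.83²) ≈ 7% lie within 0.83 km. If the 34 lie apart, both shares are zero. The scatter is an assumption, so neither figure should be read as an estimate.

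It is also tempting to infer further unbuffered VEA villages from the Introduction, which says the programme "will offer an extended VEA programme to an additional 240 villages and 60 schools in 5 provinces": 146 + 34 + 30 = 210, leaving 30. The documents do not support this. The 240 is a forward-looking programme total over five provinces, and no North Kivu target is given. The annex requires treatment villages to match the target in each province, which makes 146 in the four study provinces. Nothing places any further village near a control.

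**Conclusion.** The gap holds as a matter of text: the 2.5 km separation does not extend to the 34 villages, and the 2 km check is blind to them in Kasai Central unless they are counted. The consequence is conditional. If control households use water points in those villages, the effect is diluted toward zero. The loss could be large for the Kasai Central subgroup and is modest for the pooled estimate, which keeps about 88% or more of its value for f up to 0.50. These figures rest on province-level weights, an assumed f, and working VEA points in the 34 villages by midline. Proximity alone does not show use, and the documents give no distances, so the true share may be nil. A reader might compare the 35% of control villages with the pooled result and infer a large bias. Stratum adjustment reduces the relevant weight to about 17% to 23%. The point is worth acting on because the uncertainty can be narrowed with data already held.

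**What to change.** 1. Using the coordinates held for the 403 villages, compute the distance from each Kasai Central study village to the nearest of the 34, and report the distribution by arm.
2. State in the spillover section that the 34 count as intervention villages in the exposure measure, and use a 2.5 km radius in Kasai Central.
3. Pre-specify a sensitivity analysis of the four primary outcomes that drops, in both arms, study villages within 2.5 km of any of the 34. This distance was fixed before randomisation, so the exclusion keeps the randomised comparison.
4. Read the Kasai Central subgroup result alongside that analysis.

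The cost is one distance calculation and one extra analysis, with no new data collection. Intervals in the sensitivity analysis will be somewhat wider, most of all within Kasai Central, which has only 8 treatment clusters. If no study village lies within 2.5 km of the 34, a sentence saying so closes the matter.

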## Survey rounds and timeline

We plan to conduct two major rounds of household surveys: (i) a midline survey at least 12 months after the start of implementation: surveys of village leadership, WASH infrastructure, and selected households in treatment and control clusters to capture medium-term effects on main implementation outcomes such as access to improved water sources, quality of water, access to and use of improved latrines and diarrhea; and (ii) an endline survey at least 24 months after the start of implementation: surveys of village leadership, WASH infrastructure, and selected households in treatment and control clusters to capture longer-term effects.

We did not carry out a baseline prior to the rollout of project activities due to operational and timeline constraints.

